## Abstract

**Background:**

A large number of individuals suffer from post-COVID-19 condition (PCC), characterised by persistent symptoms following a SARS-CoV-2 infection with an impact on daily personal and professional activities. This study aims at examining which (health) care services are used by PCC patients in the German federal state of Lower Saxony, and how these patients manage their condition. The perspectives of patients, informal caregivers and general practitioners (GPs) will be considered.

**Methods:**

The study will employ a mixed methods design. Patients’ perspective will be evaluated through an online survey of: (1) 21,000 adult individuals with a PCC diagnosis (ICD10 U09.9!) in their statutory health insurance claims data in 2022 (“AOK survey”) and (2) a self-selected sample of adult individuals with a proven SARS-CoV-2 infection in 2023 and persistent symptoms (“public survey”). Additional data sources will be claims data (n = 27,275) and 25–30 semi-structured interviews. Informal caregivers_’_ perspective will be collected through an online survey and semi-structured interviews. GPs’ perspective will be evaluated through four focus groups involving six to eight participants each and an online survey of all registered and practicing GPs in Lower Saxony (approximately 5,000). All survey data will be descriptively analysed. In addition, correlation analyses and multivariable regression analyses will be conducted, for example on factors influencing affected individuals’ use of medical services. Interview and focus group data will be subjected to qualitative content analysis. A health economic analysis will be used to determine the costs of PCC to health care payers, patients and society. The project will conclude with an expert workshop to discuss the results and derive recommendations.

**Discussion:**

The results of the study will provide a multidimensional description of the (health) care situation and needs of patients with PCC, and derive recommendations for improving health care.

**Trial registration:**

The VePoKaP study is registered at the German Clinical Trials Register (DRKS00032846).

## Introduction

In recent years, the SARS-CoV-2 pandemic has placed global health care systems and societies under tremendous pressure. A COVID-19 disease can have far-reaching consequences, including symptoms that persist well beyond the acute infection and affect not only persons who were severely ill, but also those who had only mild symptoms initially [1]. The WHO defines these persistent complaints as a post-COVID-19 condition (PCC), which “occurs in individuals with a history of probable or confirmed SARS-CoV-2 infection, usually 3 months from the onset of COVID-19 with symptoms that last for at least 2 months and cannot be explained by an alternative diagnosis. Common symptoms include fatigue, shortness of breath, and cognitive dysfunction, and generally have an impact on everyday functioning” [2]. PCC, and especially fatigue as a frequent occurring symptom of PCC, has a significant impact on individuals’ physical and mental wellbeing, thereby affecting their daily personal and professional activities [3].

Estimates of PCC prevalence vary widely, ranging from 2.3% to 16% for non-hospitalised patients [4]. However, it is currently being discussed that methodological flaws have led to a significant overestimation of PCC prevalence in many scientific publications [5, 6]. Notwithstanding this potential overestimation, the number of individuals affected by PCC is likely high, given the exceptionally high number of people who have been infected with SARS-CoV-2. Thus, even considering a low prevalence rate, PCC represents a significant burden on health care systems and societies, worldwide [7].

A study in the USA found that the direct medical costs associated with PCC in the first 6 months of persistent symptoms (i.e., starting 31 days after SARS-CoV-2 infection) were 1.46 times higher than those for controls with no equivalent SARS-CoV-2 infection [8]. Additionally, PCC is associated with indirect costs due to productivity losses—either through time off work, presentism or disability. In Germany alone, a study projected the overall economic, health care and pension costs associated with PCC with an onset in 2021 at approximately 7.4 billion euros [9]. Furthermore, PCC gives rise to social and societal costs due to the burden that is placed on relatives and friends. The functional limitations associated with PCC impact patients’ social lives and fulfilment of everyday tasks [3, 4], thereby necessitating the support services of informal caregivers (non-professional persons (both kin and non-kin caregivers like neighbours and friends) who provide care in a home setting). This aspect has not yet been sufficiently addressed in the literature.

General practitioners (GPs) are typically the first point of contact for patients with persistent symptoms following a SARS-CoV-2 infection. Thus, they play a key role in the management of PCC patients [10–12]. Although PCC is characterised by certain common symptoms, its clinical presentation remains extremely heterogeneous [13]. Accordingly, GPs report substantial uncertainty in their diagnosis and treatment of the condition [11, 12, 14]. As other possible causes for the symptoms must be ruled out, it is often the case that patients are assessed by different medical specialists, making the diagnosis and treatment process very time-consuming (for both the affected individuals and GPs) [12, 14]. The high level of suffering experienced by patients, combined with a lack of well-established and effective therapies, can also lead patients to visit many different medical specialists to try new therapeutic approaches [15]. Such approaches may include conventional medical treatments as well as complementary and alternative medical procedures. Little is known about the health care services utilised by PCC patients and their pathways through the health care system. As a proportion of affected individuals do not appear to fully recover over the long term [16, 17], it is important to evaluate how they manage their symptoms and complaints.

The present protocol describes the study “Care for patients with post-COVID: Analysis of claims data and the perspectives of patients, informal caregivers and general practitioners (VePoKaP)” [German: Versorgung von Patient*innen mit Post-COVID: Analysen von Kassendaten und von Perspektiven der Patient*innen, Angehörigen und Hausärzt*innen (VePoKaP)] registered at the German Clinical Trials Register (DRKS00032846). The study findings will be used to derive recommendations for improving the care of individuals affected by PCC in Lower Saxony, a German federal state comprised of rural, urban and metropolitan regions. Additionally, as both hospital planning and outpatient care management are conducted at the federal state level, the federal state approach of the present study may best support a successful science-practice-policy transfer.

### Objectives

The study aims at evaluating individuals affected or formerly affected by PCC in Lower Saxony, with respect to their use of health care services and management of their complaints. In doing so, the research will consider the perspectives of individuals at different stages of PCC and with different levels of PCC severity, as well as those of informal caregivers and GPs.

The following research questions will be answered:

Perspective of affected and formerly affected individuals
1) Which health care services are used by PCC patients? To what extent are complementary and alternative services used? Are there regional differences in Lower Saxony (comparison of rural, urban and metropolitan regions)? How satisfied are PCC patients with the health care services available to them? Which health care services are lacking?2) What strategies do affected individuals use to cope with PCC at work and in everyday life? How important is support from informal caregivers?3) Is there an association between the severity of PCC and the ways in which affected individuals cope with their symptoms, the ways in which affected individuals use health care services, or the needs of affected individuals?Perspective of informal caregivers
4) How do informal caregivers experience and cope with the disease? What is their caregiver burden and what support do they need?Perspective of GPs
5) How do GPs rate the health care of individuals with PCC and their use of health care services in terms of the diagnostic process, availability and quality of treatment options and improvement in health status? How do GPs perceive individuals with PCC to be coping with the disease? What do GPs identify as the health care needs of individuals with PCC?Health economic perspective
6) What are the costs of PCC from the perspective of health care payers, patients and the society? What is the economic impact of PCC on the affected persons and their informal caregivers?

## Materials and methods

The study employs a mixed methods design, integrating quantitative and qualitative methods of health services research, secondary data analysis and health economic analysis (Fig 1).

**Fig 1 pone.0316335.g001:**
[figure not shown]
Study design: Perspectives and data collection methods. © [name] via Canva.com. ^a^ individuals who have statutory health insurance with the AOK Lower Saxony; ≥ 18 years old; post-COVID-19 condition (ICD10 U09.9) in their outpatient billing data or certificates of incapacity for work (claims data) in 2022; place of residence: Lower Saxony; continuously insured with the AOK Lower Saxony since 2019; no individuals whose affairs are managed by a guardian; no employees of the AOK Lower Saxony. ^b^ Persons with SARS-CoV-2 infection (self-test sufficient) in 2023 and persistent symptoms in self-perception; ≥ 18 years old; place of residence: Lower Saxony.

### Data collection

#### Perspective of affected and formerly affected individuals

The perspectives of individuals affected or formerly affected by PCC will be assessed through two separate cross-sectional online surveys and an evaluation of claims data from the largest statutory health insurance company in Lower Saxony (AOK Lower Saxony), which covers one-third of the adult population (2,370,541/6,676,314) [18]. In addition, semi-structured interviews will be conducted (Fig 1).

For the first online survey (AOK survey), adult individuals meeting the following inclusion criteria will be invited by post to participate in the research: (a) insured with AOK Lower Saxony, (b) diagnosed with PCC (ICD10 U09.9) in their claims data (outpatient billing data or a certificate of incapacity for work in 2022), (c) resident of Lower Saxony and (d) continuously insured with AOK Lower Saxony since 2019. Individuals whose affairs are managed by a guardian or who are employees of the health insurance company will be excluded, resulting in a final sample of 27,275 (AOK claims data group). For budgetary reasons, a random sample of 21,000 insured persons will be selected and included (AOK survey group). The invitation will contain a link to the online questionnaire and a randomly assigned individual identification number (ID), serving as an access code. The ID will also be included in the AOK Lower Saxony claims data, to create a personal link between the primary online survey data and the secondary claims data for the analyses. To maximise the response rate, a reminder letter will be sent to individuals who have not completed the survey after 2 weeks. In addition, telephone support will be offered to clarify open questions and solve technical problems. Assuming a response rate of 25%, *n* = 5,000 participants are expected.

Given the criterion of a PCC diagnosis in 2022, the AOK survey sample is likely to include both individuals who remain affected by PCC at the time of the survey completion (affected individuals) and individuals who have already recovered (formerly affected individuals). In order to be able to address the participants appropriately, the survey will begin with the question of whether the person still has symptoms or whether they have already recovered. Depending on the answer, the following questions are then asked in a customised form with the help of a filter guide. For example: “How often are you currently restricted in carrying out your normal everyday tasks (e.g. household, grocery shopping, childcare,…) due to your post-COVID symptoms?” vs. “How often were you restricted in carrying out your normal everyday tasks (e.g. household, grocery shopping, childcare,…) due to your post-COVID symptoms?” The reference year of 2022 was chosen because outpatient billing data in Germany are only available from statutory health insurance funds with a time lag of about 9 months. However, this reference year will also ensure that the findings of the AOK survey on the development of symptoms, the need for treatment and the utilisation of medical services refer to a significant period of time.

The selection of patients for the AOK survey is based on a medical PCC diagnosis, which is generally considered trustworthy. However, it is also possible to validate this secondary data against the primary data from the AOK survey to ensure that only people who have had a previous SARS-CoV-2 infection and whose symptoms have persisted for three months according to the WHO definition are actually included in the analyses.

To recruit participants for the second online survey (public survey), AOK Lower Saxony will launch a public call via its social media channels and member magazine. Eligible participants meet the following criteria: (a) tested positive for SARS-CoV-2 in 2023 (self-test sufficient), (b) report persistent symptoms and (c) reside in Lower Saxony (group 2). Interested individuals will be able to access the online survey via a link or a QR code. This public survey group recruitment via self-selection will aim at reaching currently affected individuals who have not necessarily presented to outpatient or inpatient care, or have not been diagnosed with PCC by a GP or medical specialist. Despite the bias associated with self-reporting the presence of PCC symptoms, this potentially vulnerable group is considered separately. Individual questions are added to validate the self-report.

Both online surveys will include: (a) self-developed items referring to sociodemographic and socioeconomic factors, symptoms and their progression, utilisation of health care services (including complementary and alternative medical services), satisfaction with care and impairments in everyday and working life (S1 Appendix); and (b) standardised instruments (Table 1). Answering the survey is estimated to take about 30 minutes.

**Table 1 pone.0316335.t001:** Standardised instruments included in both online surveys of affected individuals.

Patient-related constructs and outcomes	Instruments
Fatigue	Chalder Fatigue Scale [19, 20]
Post-exertional malaise	DePaul Symptom Questionnaire—Post-Exertional-Malaise (DSQ-PEM) [21, 22]
Anxiety and depression	Patient Health Questionnaire (PHQ-4) [23]
Health-related quality of life	EQ-5D-5L [24, 25]
Social support	Brief Social Support Scale (BS-6) [26]
Perception of social participation	Short Scale Measuring Perceived Social Participation (KsT-5) [27]
Self-efficacy	Short form of the General Self-Efficacy Scale (GSE-6) [28]
Coping with illness	Short form of the Freiburger Fragebogen zur Krankheitsverarbeitung (FKV-15) [29]

The comprehensibility of the questionnaire will be informally verified through pretesting with colleagues and affected individuals, who complete the online survey and give feedback on each question [30].

Currently affected respondents who indicate a recovery time of 14 hours or more in the DSQ-PEM will be offered the option of psychosomatic counselling at Hannover Medical School (MHH). The goal is to make sure that these severely affected patients receive the necessary help and to support them in finding adequate treatment if needed. The number of respondents who make use of this counselling service, and the specific needs they report, will be documented.

The claims data of the 27,275 adult individuals with a PCC diagnosis in 2022 who are insured by AOK Lower Saxony (AOK claims data group) will serve as a secondary data source. The claims data of the statutory health insurers contain, in addition to the insured persons’ sociodemographic data, billing data from reimbursed healthcare services providing an overview of the services utilised by patients from the time of diagnosis, with respect to outpatient care, medication, therapeutics, inpatient care and rehabilitation, and periods of sick leave incurred. In order to chart at least 6 months of data follow-up after diagnosis, the first three quarters of 2023 will be taken into account, in addition to the year 2022. Pre-existing conditions or comorbidities will be identified in the preceding years of 2019–2021. Information on the settlement structure of the place of residence (e.g., urban/rural area) will be obtained on the basis of the classification of the Federal Institute for Research on Building, Urban Affairs and Spatial Development [31]. Where relevant, claims data will be linked to the primary survey data for any insured individual who participate in the AOK online survey.

In addition to the two online surveys and claims data, semi-structured interviews will be conducted to collect further perspectives from affected and formerly affected individuals. Eligible participants for these interviews include adult individuals with statutory health insurance who are able to participate in an interview regarding their health status in the German language. Participants will be purposefully sampled based on characteristics such as health status (i.e., affected/formerly affected), sex, age, place of residence (i.e., urban/rural) and presence/absence of informal support. This criterion sampling will allow to consider different perspectives [32–34]. An interview invitation leaflet will be sent to all statutory insured individuals of AOK Lower Saxony, alongside the invitation to the AOK online survey. Anticipating high willingness to participate, only a random sample of 25% of the total number of insured individuals contacted for the AOK online survey will be invited. Individuals who are interested in participating in the interviews will be invited to contact the research team by telephone or email. A total number of 25–30 interviews will be conducted [35, 36]. In preparation for the interviews, an interview guide on topics such as individual strategies for coping with fatigue related to PCC, experiences with primary care, met and unmet needs, and wishes for health care will be developed on the basis of the literature and discussions within the interdisciplinary research team (S3 Appendix). Prior to data collection, the interview guide will be piloted and refined, where necessary. To enable a description of the sample, interview participants will also complete a short questionnaire focused on sociodemographic factors. Half of the interviews will be conducted by a researcher from MHH and the other half by a researcher from University Medical Center Göttingen (UMG). The 30- to 60-minute interviews will be audio-recorded and conducted at MHH, UMG or participants’ homes, or via video conference or telephone.

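### The claims cohort admits any U09.9 code in 2022, not a first code, so results described as from diagnosis, and baseline comorbidity, are not well defined for anyone coded earlier

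*Protocol article*

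**What the plan says.** All of this is in the protocol article, Data collection, under the perspective of affected and formerly affected individuals, unless another place is named.

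- **Entry.** A person qualifies if "diagnosed with PCC (ICD10 U09.9) in their claims data (outpatient billing data or a certificate of incapacity for work in 2022". The Fig 1 legend gives the same rule. Neither place asks for a first code or a code-free period.
- **Insurance.** Members must be "continuously insured with AOK Lower Saxony since 2019".
- **Exclusions.** "Individuals whose affairs are managed by a guardian or who are employees of the health insurance company will be excluded". No other exclusion is named, and the resulting claims group is 27,275 people.
- **What the claims are to show.** They are described as "providing an overview of the services utilised by patients from the time of diagnosis".
- **Window.** "In order to chart at least 6 months of data follow-up after diagnosis, the first three quarters of 2023 will be taken into account", together with the year 2022.
- **Earlier years.** Claims from 2019 to 2021 are used to identify pre-existing conditions or comorbidities. No other use of them is stated.
- **Disease before 2022.** The Introduction cites a German projection of "economic, health care and pension costs associated with PCC with an onset in 2021" and notes that some patients do not recover fully in the long term.

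**The concern.** The entry rule selects people who carry a code in a calendar year, whenever it was first given. The follow-up wording and the role of the earlier years treat 2022 as the year of diagnosis. The two agree only for people whose first code falls in 2022.

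For someone first coded in 2021 and coded again in 2022, two things go wrong. Services in the first months after diagnosis fall before the window opens. Those same months also lie in the years used to define baseline, so a condition recorded in 2021 as part of the post-COVID illness could be listed as pre-existing.

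This matters because the Introduction motivates the study partly by how little is known about patients' routes through the health care system, and describes a long diagnostic phase involving several specialists. That phase is what the window would miss for an earlier-coded patient.

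**Working it through.** **Step 1: reproduce the plan's own figure.** The plan says "In order to chart at least 6 months of data follow-up after diagnosis". The window closes on 30 September 2023. Using 30.4375 days per month:

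- Diagnosis on 31 December 2022: 273 / 30.4375 = 9.0 months of follow-up.
- Diagnosis on 1 January 2022: 637 / 30.4375 = 20.9 months.

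So the six-month minimum holds for every diagnosis dated in 2022.

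**Step 2: the same window for a first code in 2021.** The time after diagnosis that falls before 1 January 2022 is:

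- First code on 1 January 2021: 365 / 30.4375 = 12.0 months.
- First code on 1 July 2021: 184 / 30.4375 = 6.0 months. The window then covers roughly months 6.0 to 27.0 after diagnosis (184 + 637 = 821 days; 821 / 30.4375 = 27.0).
- First code on 31 December 2021: 1 / 30.4375 = 0.03 months.

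The July example shows that a check on length of follow-up would not reveal the problem. More than six months are observed, but none of them belong to the first six after diagnosis.

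**Step 3: can such people be in the cohort?** The entry rule and exclusions do not keep them out. The Introduction makes them plausible: disease with onset in 2021, and incomplete recovery in some patients. It does not show that U09.9 was recorded in 2021, or how often a code was repeated in 2022.

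**Step 4: how many?** The document gives no figure, so what follows is illustration only.

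| Assumed share first coded before 2022 | Prevalent, of 27,275 | Newly coded in 2022 |
|---|---|---|
| 5% | 1,364 | 25,911 |
| 20% | 5,455 | 21,820 |
| 40% | 10,910 | 16,365 |

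A simple model gives values inside this range. Assume first codes arrive steadily within each year, coding lasts an exponential time with mean D years, and 2021 incidence is k times that of 2022. Per unit of 2022 incidence, the number still being coded on 1 January 2022 is p = k × D × (1 − exp(−1/D)), and the prevalent share is p / (1 + p).

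- k = 1, D = 0.25: p = 0.25 × (1 − exp(−4)) = 0.245; share 19.7%, or 5,375 people.
- k = 1, D = 1: p = 1 − exp(−1) = 0.632; share 38.7%, or 10,564.
- k = 0.5, D = 0.25: p = 0.123; share 10.9%, or 2,981.
- k = 0.5, D = 1: p = 0.316; share 24.0%, or 6,550.

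Neither k nor D comes from the document.

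**Step 5: does anything else in the article resolve it?** The planned check of claims against survey answers concerns prior infection and three-month persistence, not the date of first diagnosis, and reaches survey respondents only. The limitations in the Discussion cover response bias, recall and generalisability, not mixed time since diagnosis.

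**The case against.** The strongest reply is that a mixed cohort is the design. The Objectives ask for people at different stages of the condition, and the Data collection section expects both current and recovered patients and defends 2022 as the reference year. For which services are used, regional differences and costs, everyone coded in a reference year is a proper frame, and a washout would remove patients whom the study wants. This stands, and it is why the sample should not change.

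The wording about services from diagnosis also describes what claims data contain and sets no formal index date. A fuller analysis plan may set one, and the stated use of 2019 to 2021 does not rule out others. This too stands, and it lowers the weight of the point. It does not remove it, because the article itself fixes the entry rule, the window and the earlier years as baseline, and those three do not fit together for an earlier-coded person. Survey items on symptoms and their progression give some information on disease duration, but only for respondents.

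A reader might go further and infer that many of the 27,275 were certainly coded in 2021, and that the results will therefore understate early specialist contacts and overstate persistence and chronic use. The document does not support this. Onset in 2021 is not the same as a U09.9 claim in 2021, no share can be derived, and the Data analysis section names no time-since-diagnosis or persistence analysis whose bias could be signed or sized.

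**Conclusion.** The point holds in a limited form. The entry rule admits prevalent cases, while the follow-up wording and the baseline years presuppose incident ones. Per affected person, up to 12 months of post-diagnosis care would be lost for a first code in 2021, and those months would be read as baseline. The number of people affected is unknown, and every percentage above is an assumption.

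The conclusion rests on two premises: that some members had a U09.9 code before 2022, which is plausible but not shown, and that results will be presented as from or after diagnosis, as the article's wording suggests. Descriptions of service use and cost in the reference period are not affected.

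**What to change.** Keep all 27,275 and make these changes to the claims analysis:

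1. Search each member's 2019 to 2021 claims for U09.9 and date the diagnosis at the first code found.
2. Flag each person as incident (no code before 2022) or prevalent (coded before 2022), and report the share of each.
3. Base results described as from or after diagnosis on incident cases, and show prevalent cases separately.
4. Count as pre-existing only conditions recorded before the first U09.9 code.

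The cost is small. Continuous insurance since 2019 is already required and claims from those years are already to be used, so the work is a derived date, a flag and a stratified table, with no new recruitment. If no earlier codes are found, the search settles the matter. If many are found, the group for the from-diagnosis results shrinks and those estimates lose some precision.

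### The fixed 2019–2021 look-back includes post-infection time for people infected before 2022, so early PCC symptoms can be recorded as pre-existing comorbidity in a subset of unknown size

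*Protocol article*

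**What the plan says.** All the relevant claims rules are in the Protocol article, Data collection, under the perspective of affected and formerly affected individuals.

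- **Look-back:** "Pre-existing conditions or comorbidities will be identified in the preceding years of 2019–2021". The same three calendar years apply to everyone.
- **Entry:** insured adults "diagnosed with PCC (ICD10 U09.9) in their claims data (outpatient billing data or a certificate of incapacity for work in 2022", with continuous AOK membership since 2019. The article states neither a first-code rule nor an infection-date rule for this cohort.
- **Service data:** the claims are described as "providing an overview of the services utilised by patients from the time of diagnosis". For the observation period, "the first three quarters of 2023 will be taken into account, in addition to the year 2022".
- **Timing of PCC:** the Introduction cites the WHO definition, "usually 3 months from the onset of COVID-19 with symptoms that last for at least 2 months and cannot be explained by an alternative diagnosis".
- **Check on the diagnosis:** the article says it is possible to validate the claims diagnosis against the AOK survey, so that only people with a previous infection and "whose symptoms have persisted for three months according to the WHO definition are actually included in the analyses". This can reach survey respondents only.

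**The concern.** A condition is pre-existing if it was present before the infection. The plan sets the boundary at 31 December 2021 for everyone, whatever the infection date. The boundary is then wrong in one of two directions. For a person infected in 2020 or 2021 it falls too late, and fatigue, breathlessness or low mood first coded after the infection counts as old. For a person infected during 2022 it falls too early, and a condition first coded that year before infection is not captured.

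What is at stake is the separation of old from new morbidity. That separation enters the description of the cohort, and it would enter any model of service use or severity that uses comorbidity. It matters more here because the Discussion concedes that some participants may not know whether their symptoms predate the infection, and looks to claims data to offset weaknesses of the individual data sources. For people infected before 2022, the look-back as written cannot settle that question.

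**Working it through.** **Inputs from the article:** cohort 27,275; U09.9 code at any time in 2022; look-back 1 January 2019 to 31 December 2021 (36 months); services from 2022 and the first three quarters of 2023; usual lag from infection to PCC of 3 months.

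**Assumptions, because the article gives neither distribution:** diagnosis dates spread evenly over 2022, and one fixed lag of L months from infection to diagnosis.

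**Step 1, the plan's own figure.** The article states at least 6 months of follow-up after diagnosis. The latest diagnosis is 31 December 2022 and data end on 30 September 2023: 273 days, or 273 / 30.44 = 9.0 months. The stated minimum holds.

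**Step 2, who overlaps.** Infection date = diagnosis date − L. It falls in the look-back when the diagnosis comes within the first L months of 2022. For L up to 12:

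- share with overlap = L / 12
- mean overlap among those affected = L / 2 months
- share of all infection-to-diagnosis time inside the look-back = (L/12 × L/2) / L = L / 24

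| Lag L (months) | Share with overlap | Of 27,275 | Mean overlap (months of 36) | Share of infection-to-diagnosis time in look-back |
|---|---|---|---|---|
| 2 | 17% | about 4,500 | 1.0 | 8% |
| 3 | 25% | about 6,800 | 1.5 | 13% |
| 6 | 50% | about 13,600 | 3.0 | 25% |
| 9 | 75% | about 20,500 | 4.5 | 38% |
| 12 | 100% | 27,275 | 6.0 | 50% |

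Lags longer than 3 months are plausible on the article's own account: the Introduction says that other causes must first be excluded, often by several specialists, "making the diagnosis and treatment process very time-consuming". Shorter lags are possible too, because the definition says usually. The overlap is a small part of the 36 months, but it is the part straight after infection, when new symptoms would first be coded.

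**Step 3, the opposite error.** The remaining share, 1 − L/12, is infected during 2022. Their pre-infection time in 2022 lies outside the look-back and averages (12 − L) / 2 months. At L = 3 that is 75% of the cohort and 4.5 months; at L = 6 it is 50% and 3.0 months.

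**Step 4, services before diagnosis.** By the last column, at a 3-month lag about 87% of infection-to-diagnosis time falls in 2022, a year whose claims are used for services. The other 13% falls before 2022, in years that the article mentions only for comorbidity.

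**The case against.** The strongest reply is that a journal article condenses the full protocol. Index dates, the comorbidity algorithm and a prevalent-case flag are commonly left to that document, and identifying conditions in 2019–2021 does not rule out using dates within those years. This has weight for the details. It does not remove the point, because the article states the window itself, and as stated the window does not depend on infection.

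Three stronger readings are tempting, and the documents do not support them.

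- **Work-up excluded.** A reader might infer that the diagnostic work-up is dropped from pathways and costs, since the services are described from diagnosis onwards. But that phrase describes what the claims contain. It does not say only, the whole of 2022 is used, Data analysis gives no start date for costs, and the survey also asks about service use. What stands is that the treatment of services between infection and diagnosis is not stated, and that work-up done before 2022 is not addressed.
- **PCC effect removed.** A reader might infer that adjusting for contaminated comorbidity takes away part of the effect of PCC. No comparator without PCC is stated, so there is no such effect to attenuate. Data analysis does not name comorbidity as a covariate either.
- **At least a quarter affected.** A reader might take 25% as a floor. It rests on evenly spread diagnoses and a fixed 3-month lag, and the article itself allows that some coded patients may not meet the three-month criterion.

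**Conclusion.** The point holds in limited form. The article's look-back ends on a fixed date, while eligibility follows the year of a PCC code, so people infected before 2022 have post-infection time counted as history. Early PCC symptoms *can* be recorded as comorbidity in this subset; the documents do not show that they generally are. People infected in 2022 are exposed to the reverse error.

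The size is unknown. The 17%, 25% and 50% at lags of 2, 3 and 6 months depend on even spacing of diagnoses and a single lag. They count people whose window overlaps, not people with a misclassified condition. Cases first coded before 2022, if any, have longer overlaps than these lags imply. The consequence is blurred old and new morbidity in the cohort description and in any utilisation or severity model that uses comorbidity. The article should correct this before the claims variables are built.

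**What to change.** 1. End each person's look-back before the quarter of the coded SARS-CoV-2 infection that precedes the first U09.9 code. Where no infection is coded, use the quarter before the first U09.9 code as the anchor.
2. Flag people whose first U09.9 code precedes 2022 as prevalent.
3. Repeat the analysis with a 2019-only look-back as a sensitivity analysis. It should not replace the main rule: it excludes post-infection time for anyone infected from 2020 onwards, but it also discards 2020 and 2021 for people infected in 2022 and so worsens the missed-comorbidity error for them.
4. Where claims services are counted, include those between infection and diagnosis, or report them separately.

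The cost is mainly re-programming. The plan already uses 2019–2021 claims and requires continuous insurance since 2019. Item 4 needs service records from before 2022 for some people; whether the existing extract holds them should be checked. The downsides are unequal look-back lengths between persons, and reliance on the fallback for uncoded infections or reinfections. The fallback is itself an assumed lag, so the number of people placed by it should be reported.
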